### Sample size

2.6

Because of the importance of the ECSP-I in this project as a behavioural outcome tool for obtaining quantitative data through technology, we calculated the sample size to detect associations between the ECSP-I score and the groups (1, 2 and 3) at each time point. The calculation was based on preliminary data (not already published) from the Italian ESCP (ECSP-I) version. A standard deviation of 0.56 is assumed for the ECSP-I scale, and the significance level is *α* = 0.01, obtained by applying the Bonferroni correction for multiple comparisons, performed in pairs between groups, to the type I error; we obtained a sample size of 14 subjects per group to detect a difference of 0.8 between the means of each group using a 2-tailed Student's *t*-test for independent samples, with a power of 80%. Assuming a drop-out rate of 15%, the required sample size increases to 16 subjects per group, that is, 48 subjects in total.

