### Recruitment

2.2

Families will be recruited via advertisements distributed through several Fondazione Don Gnocchi (FDG) branches in Lombardia, Italy. The study will be performed in the most important department of Fondazione Don Gnocchi, which is the scientific institute IRCCS Santa Maria Nascente in Milano; this is one of the leading Italian healthcare centres for the diagnosis and rehabilitation of children with neurodevelopmental disabilities. Siblings of TD children will be recruited with the help of daycares in the same area. All families will be recruited during pregnancy or until the infant reaches 8 months of life and will be followed over the following 12 months.

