### Inclusion criteria

2.3

Participants have to meet the following inclusion criteria: (1) the infant must have one or more biological siblings; (2) the child must not be more than ten months of age at the time of the first assessment; (3) the child must undergo a normal neurological examination; (4) parents must agree to the assessment requirements; and (5) the parents must have sufficient Italian language to complete the assessments.

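### The only test stated for the ECSP-I is an unadjusted pairwise t-test, although the non-randomised groups can differ in age at assessment; age should be a covariate

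*Protocol article*

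**What the plan says.** All places are in the protocol article.

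- **Test.** Section 2.6 (Sample size) sizes the trial on the ECSP-I: "we calculated the sample size to detect associations between the ECSP-I score and the groups (1, 2 and 3) at each time point". The comparison is pairwise, "using a 2-tailed Student's *t*-test for independent samples, with a power of 80"%, and "the significance level is *α* = 0.01, obtained by applying the Bonferroni correction for multiple comparisons". The target difference is 0.8. On variability: "A standard deviation of 0.56 is assumed for the ECSP-I scale". This comes from unpublished preliminary data whose age range is not given. Section 2.13 (Statistical analysis) names no ECSP-I model and no age term; it refers only to standard trial methods for comparing the three groups.
- **Instrument.** Section 2.5.1.1 lists the ECSP-I among the main outcome measures and describes it for children of 3 to 30 months. It does not say whether the analysed score is age-standardised.
- **Groups.** Section 2.11 (Study procedures) forms the groups from sibling status and T0 scores on the Griffiths-3 and the CSBS checklist. There is no randomisation.
- **Recruitment.** Section 2.2 reaches families through the institute's branches, but "Siblings of TD children will be recruited with the help of daycares in the same area".
- **Age at T0.** Section 2.2: "All families will be recruited during pregnancy or until the infant reaches 8 months of life". Section 2.3: "the child must not be more than ten months of age at the time of the first assessment". The Abstract and section 2.11 place T0 within 8 months of life. No lower limit is stated.
- **Visit timing.** Section 2.1 counts T1 and T2 from T0. Section 2.11 counts them from the start of the intervention, which for Groups 2 and 3 may fall up to one month after T0 and which Group 1 does not have.

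**The concern.** A scale meant to cover 3 to 30 months of early communication can be expected to change with age unless its scores are age-standardised. An unadjusted comparison of group means then carries any difference in mean age straight into the estimated group difference. Randomisation would make such a difference a matter of chance, already allowed for in the test's error rate. Here nothing in the allocation balances age, one group is found through a separate channel, and the visit rules can themselves shift age at T1 and T2 between Group 1 and the other two groups.

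The bias could go either way: it could mimic a group difference or hide one. The comparisons affected are those on which the whole sample size rests. Age follows from the birth and visit dates, so leaving it out gains nothing.

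**Working it through.** **1. The plan's own figure.** Inputs from section 2.6: difference 0.8, SD 0.56, two-sided alpha 0.01, power 80%.

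- Standard error of a pairwise difference at n = 14: 0.56 × √(2/14) = 0.212.
- Noncentrality: 0.8 / 0.212 = 3.78, with 26 degrees of freedom and critical value 2.779.
- Power from the noncentral t distribution: 83.1% at 14 per group and 79% at 13. So 14 is the smallest n reaching 80%.
- Dropout: 14 × 1.15 = 16.1, the stated 16 per group. Dividing instead, 14 / 0.85 = 16.5, gives 17, which is immaterial here.

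The sample-size arithmetic is not at fault.

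**2. How wide age at T0 can be.** Taken literally, the text runs from birth to 8 or 10 months. But allocation at T0 needs the CSBS checklist, described for 6 to 24 months. If that tool is used within its range, T0 falls at about 6–8 or 6–10 months. For a uniform distribution the SD is width/√12, so 2/√12 = 0.58 or 4/√12 = 1.15 months. With the ECSP-I's own lower limit of 3 months, the window 3–10 gives 7/√12 = 2.02 months.

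**3. Bias from an age gap.** Bias = slope × difference in mean age. The slope is an assumption (0.05, 0.10 or 0.20 points per month), because the documents give none. The false-positive rate is the probability that the nominal 1% test rejects when the only difference between the groups is this bias (noncentral t, n = 14, SD 0.56).

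| Slope (points/month) | Age gap (months) | Bias | Share of 0.8 | False-positive rate |
|---|---|---|---|---|
| 0.05 | 1 | 0.05 | 6% | 1.2% |
| 0.10 | 1 | 0.10 | 12.5% | 1.8% |
| 0.20 | 1 | 0.20 | 25% | 4.6% |
| 0.05 | 2 | 0.10 | 12.5% | 1.8% |
| 0.10 | 2 | 0.20 | 25% | 4.6% |
| 0.20 | 2 | 0.40 | 50% | 21% |

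A 1-month gap is a reasonable reference, because the conflicting visit anchors alone could produce up to about that much at T1 and T2. A 2-month gap is extreme if T0 lies at 6–8 months: one whole group would have to be 6 months old and the other 8. Masking is the mirror image: a bias of 0.20 against a true 0.8 leaves 0.6 and lowers power from 83% to 53%.

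**4. Error variance.** Two readings of the 0.56 are possible.

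- If it already contains the age spread, planned power stands. Age adjustment would lower the residual SD to √(0.56² − (slope × age SD)²): 0.559–0.548 for T0 at 6–8 months, and 0.551–0.388 for 3–10 months.
- If it is the SD at a fixed age, the unadjusted SD is √(0.56² + (slope × age SD)²). That gives 0.561–0.572 and power 83–81% for 6–8 months, 0.563–0.606 and 83–76% for 6–10 months, and 0.569–0.691 and 82–62% for 3–10 months.

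**The case against.** - **The t-test is a planning device.** It appears only in the sample-size section, and a statistical analysis plan that is not shown may adjust for age. This stands to the extent that the t-test cannot be called the confirmed final analysis. It is nevertheless the only test the document states for a main outcome, and the age limits and visit anchors that make age matter are contradictory in the document itself.
- **Nothing shows an age gap.** One recruitment window applies to all families, and help from daycares says nothing about the infants' age. This is correct: the direction and size of any gap are unknown. The point is that it may arise and the stated test would not handle it.
- **The score may be age-standardised.** If so, most of the concern goes. The document does not say.
- **Stronger readings a reader might infer.** One is that T0 spans most of the first 8 to 10 months and the false-positive rate is around 9%. That needs an age SD of 2 months, a score-age correlation of 0.5 and group means a full 2 months apart. On that same model, a gap of half an SD gives 1.5 to 4.4% for correlations of 0.3 to 0.7, and the checklist's age range points to a narrower window. Another is that the trial is underpowered through inflated error variance. That does not follow if 0.56 already includes age spread.
- **Baseline adjustment.** It is tempting to add T0 ECSP-I as a covariate at T1 and T2. Groups are formed from T0 developmental scores, so baseline adjustment across non-equivalent groups is open to Lord's paradox and changes the question being asked. This objection stands in full.

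**Conclusion.** The point holds as an inexpensive improvement, not as an error in the sample size. The one test stated for the ECSP-I ignores age at assessment in a design where groups are non-randomised, differently recruited, and subject to inconsistent age limits and visit anchors. If scores are not age-standardised, a 1-month gap produces a spurious difference of 0.05 to 0.20 and a per-pair false-positive rate of 1.2 to 4.6% instead of 1%. At the low end this is negligible; at the high end it is a quarter of the target difference. The slopes and gaps are assumptions, and only the design features that permit a gap are documented.

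The documents do not support a claim that planned power is wrong. Nor would age adjustment make the groups comparable: Group 3 is selected on signs of concern, and that confounding remains.

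**What to change.** 1. Compare the ECSP-I between groups with a linear model that includes age at assessment as a covariate at every time point, or analyse age-standardised scores if they exist. Keep the same pairwise contrasts and alpha.
2. Label the t-test in section 2.6 as the planning approximation, and state the age range behind the SD of 0.56.
3. Reconcile the T0 age limit (Abstract and sections 2.2, 2.3 and 2.11) and the starting point for T1 and T2 (sections 2.1 and 2.11), including what it means for Group 1.
4. Do not make T0 ECSP-I a default covariate; at most report it as a sensitivity analysis.
5. State that age adjustment does not address other confounding from the allocation.

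The cost is one degree of freedom and a few sentences. No new data are needed.

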### Trial design

2.1

The study is a controlled trial following the Consolidated Standards of Reporting Trials (CONSORT) guidelines. After enrolment and baseline assessments (T0), the children will be allocated to one of three groups:
Group 1—Clinical Monitoring Group (CM): Siblings of TD children with no signs of concernGroup 2—Active Monitoring Group (AM): Siblings of ASD children with no signs of concernGroup 3—Early Intervention Group (EI): Siblings classified as “with signs of concern” at the baseline evaluation.

All children will be re-evaluated after 6 months (T1) and 12 months (T2) from T0. Figure 1 depicts the CONSORT flow chart.

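### Alpha of 0.01 in section 2.6 is not the Bonferroni value for three pairwise group comparisons (0.0167); alpha, n and power should be restated together, and the error is conservative

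*Protocol article*

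**What the plan says.** Section 2.6 (Sample size) bases the calculation on the ECSP-I: "we calculated the sample size to detect associations between the ECSP-I score and the groups (1, 2 and 3) at each time point". It then states that "the significance level is *α* = 0.01", and gives the origin of that value as "obtained by applying the Bonferroni correction for multiple comparisons, performed in pairs between groups, to the type I error".

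The other inputs are explicit. "A standard deviation of 0.56 is assumed for the ECSP-I scale", and the aim is "to detect a difference of 0.8 between the means of each group using a 2-tailed Student's *t*-test for independent samples", at 80% power. The result is 14 per group, raised to 16 per group (48 in total) for 15% drop-out.

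Section 2.1 (Trial design) fixes three groups and three assessments: baseline (T0), then "All children will be re-evaluated after 6 months (T1) and 12 months (T2) from T0".

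The article does not give the familywise error from which the correction starts, the divisor used, or whether the visits are counted in the family.

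**The concern.** A Bonferroni level is the familywise error divided by the number of comparisons. The article names the comparisons (pairs of groups) and the number of groups (three), so the divisor should be three. The stated 0.01 does not follow from that.

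This is not a matter of detail left to an analysis plan. The article gives both a number and its derivation, and the two disagree. The number is also an input to the sample size, so the stated n and power inherit the problem. An analysis plan that copied 0.01 would repeat the error. One that used the correct Bonferroni value would disagree with the published sample size.

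**Working it through.** **Inputs.** From section 2.6: difference 0.8, SD 0.56, two-tailed independent-samples t-test, 80% power, alpha 0.01, 14 per group, 15% drop-out. From section 2.1: three groups and three visits. Assumed: familywise error 0.05.

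**Step 1. Reproduce the plan's n.** Standardised difference d = 0.8/0.56 = 1.4286. For n per group, the degrees of freedom are 2n − 2 and the noncentrality is d × √(n/2). At n = 14 that is 1.4286 × √7 = 3.78 on 26 degrees of freedom. At two-sided alpha 0.01 the noncentral t gives 83.1% power at n = 14 and 79.2% at n = 13. The stated 14 is reproduced, so 0.01 is not merely a misprint in the text.

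**Step 2. Reproduce the plan's alpha.** Three groups give 3 × 2/2 = 3 pairs.

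- 0.05/3 = 0.0167, which is not 0.01 and does not round to it.
- 0.05/0.01 = 5 comparisons, a count that the design does not have.
- Read backwards, 3 × 0.01 = 0.03, a familywise level that the article does not state.
- The Šidák value for three comparisons, 1 − 0.95^(1/3) = 0.0170, does not match either.

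**Step 3. Recalculate with the alpha that the text describes, and with the alternatives if visits were pooled.**

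| Family | Alpha | n per group for 80% power | Power at 14 per group |
|---|---|---|---|
| 3 pairs (as described) | 0.05/3 = 0.0167 | 12 (80.9%) | 88.0% |
| As stated | 0.01 | 14 (83.1%) | 83.1% |
| 3 pairs × 2 post-baseline visits | 0.05/6 = 0.0083 | 14 (81.2%) | 81.2% |
| 3 pairs × 3 visits | 0.05/9 = 0.0056 | 15 (80.7%) | 76.6% |

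An n of 14 also comes out at 0.0083, so n alone does not identify the alpha used. The article says 0.01, however, and neither 0.0167 nor 0.0056 leads to 14.

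**Step 4. Check the effect of drop-out on the described family.** At alpha 0.0167, 12/0.85 = 14.1, so 15 recruited per group would be enough. The planned 16 per group leave 16 × 0.85 = 13.6 evaluable. Even at 13, power at 0.0167 is 84.8%.

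**The case against.** Three points can be made for the plan.

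*The starting level is not stated.* The sponsor may have begun from something other than 0.05, or may have taken a round number below 0.0167 on purpose. Either would be legitimate. The text, however, presents 0.01 as the result of the correction. A starting level of 0.03, which three comparisons would require, is unusual enough that it would need stating.

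*The error does no harm on the plain reading.* This stands. With three comparisons, 0.01 bounds the familywise error at 3%, and 14 per group is more than the corrected alpha requires.

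*Alpha appears only in the sample-size paragraph.* This also stands. Section 2.13 (Statistical analysis) sets no significance threshold, so the article does not show that 0.01 will be the decision rule.

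A reader might go further and infer from "to detect associations between the ECSP-I score and the groups (1, 2 and 3) at each time point" that nine tests form one family, so that 0.01 is too lenient (bound 9 × 0.01 = 9%) and the trial is underpowered. The documents do not support this. The correction is defined over pairs of groups, and nothing pools the visits; a separate family at each visit is the natural reading. The shortfall also depends on counting T0, which precedes any intervention and whose scores determine the groups (section 2.11). Hypothesis H3 does mention baseline differences between groups, but as a secondary aim. With the two post-baseline visits pooled, 14 per group still reaches 80%.

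A reader might also add Griffiths-3 and the CSBS checklist to the family, since section 2.5.1.1 lists them as main outcomes. Section 2.6 sizes the trial on the ECSP-I alone and says why. Multiplicity across outcomes may properly be left to the analysis plan.

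**Conclusion.** The stated derivation of alpha is wrong. Bonferroni over three pairs gives 0.0167, not 0.01, if the familywise level is 0.05. Because 14 per group follows from 0.01, the published alpha, n and power need correcting as a set.

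The effect is small and on the safe side: 12 evaluable per group rather than 14, or about 88% power at 14 rather than the nominal 80%. These figures take the article's difference of 0.8 and SD of 0.56 as given. Type I error inflation and loss of power are not established. They would arise only if the sponsor intends visits to share one family, and 14 per group falls below 80% power only when T0 is included, by one infant per group. Severity is minor to moderate.

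**What to change.** Amend section 2.6 to state the familywise error, the number of comparisons and whether visits share a family. For the family that the text describes, the correction is: alpha = 0.0167 per pairwise comparison (0.05/3); 12 evaluable per group for 80% power; 14 per group gives about 88%.

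If the sponsor does intend visits to share one family, section 2.6 should say so and restate power accordingly:

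- Six post-baseline tests: alpha 0.0083; 14 per group gives about 81%.
- Nine tests including T0: alpha 0.0056; 14 per group gives about 77%, and 15 evaluable would be needed.

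If 0.01 was a deliberately stricter choice, it can stay, but it should be described as such (familywise bound 3%) and not as the Bonferroni result.

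The cost is a text edit, made before outcome data are seen. For the described family, no additional infants are required.

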
Moreover, these data are consistent with findings that support the possibility of modifying neural circuitry and, consequently, functional processes through environmental enrichment in early life, providing a combination of multisensory/cognitive stimulation, increased motor activity, and enhanced social interactions and eliciting natural explorative behaviours (18). Early interventions inspired by the environmental enrichment paradigm were ecological, non-invasive, and well thought-out to enhance neuroplasticity through experience. Several research groups have investigated the profound and positive effects of intensive and multisensory stimulation during the early stages of life on the human brain and on children at risk of developing neurodevelopmental disorders (19–21). Based on these findings, Whittingham and colleagues (22) recently published the ENACT protocol (ENvironmental enrichment for infants; parenting with Acceptance and Commitment Therapy), which was the first randomised controlled trial to test a very early intervention for infants at risk of ASD (infants with one or more biological siblings or a biological parent diagnosed with ASD). This model is characterised by the application of a combination of parent-mediated very early intervention with parental mental health support within the first six months of life of high-risk infants.

Remarkably, there are no specified and shared protocols in Italy in this field, although an Italian-published case report recently suggested the importance of a pre-emptive approach (23). Based on these issues, we aimed to verify the feasibility of an early, naturalistic, parent-mediated intervention in siblings of ASD children within the Italian rehabilitation context and to analyse the effects of this model on their developmental trajectories. To study this issue, we will recruit infants at low risk since siblings of children with typical development (TD) and infants at high risk because of siblings of children affected by ASD.

Based on clinical evaluation at T0, we will divide the infants into three groups as follows:
•Infants at low risk without any signs of neurodevelopmental disorders (Group 1)•Infants at high risk without any signs of neurodevelopmental disorders (Group 2)•Infants at low or high risk with signs suggestive of neurodevelopmental disorders (Group 3).

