### Study procedures

2.11

Researchers will contact interested parents to assess eligibility and provide detailed study information. Parents will provide written consent before completing baseline assessments (T0), and based on the scores from the primary outcome measures, children will be assigned to the correct group. Infants with no signs of concern (scores at the Griffiths-3 and CSBS-ITC in the normal range), which are siblings of TD children, will be allocated to Group 1 (CM); infants with no signs of concern (scores at the Griffiths-3 and CSBS-ITC in the normal range) which are siblings of ASD children will be allocated to Group 2 (AM); infants with a quotient score below 85 using Griffiths-3 and at least one score above the “concern” cut-off using the CSBS-ITC will be allocated to Group 3 (EI). Families allocated to Groups 2 and 3 will start the intervention within one month of the baseline assessment. Families allocated to Group 1 will perform only the evaluations at different time points. Assessments will be conducted at baseline (T0), which will be when the parents give their consent and within the eight months of life of the child, after six months from the start of the intervention (T1) and after 12 months from the start of the intervention (T2). During the recruitment phase, the study's importance in developing specific guidelines for children at risk of neurodevelopmental disorders will be explained in order to improve adherence to the methodology. Participants may withdraw from the study for any reason at any time.

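### One 0.8 ECSP-I difference sizes all three group comparisons without support for Group 1 versus Group 2, and testing each pair at 0.01 is stricter than it needs to be

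*Protocol article*

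**What the plan says.** Section 2.6 (Sample size) sets the aim of the calculation: "we calculated the sample size to detect associations between the ECSP-I score and the groups (1, 2 and 3) at each time point". The inputs follow: "A standard deviation of 0.56 is assumed for the ECSP-I scale", and "the significance level is *α* = 0.01", the latter "obtained by applying the Bonferroni correction for multiple comparisons, performed in pairs between groups". The result is that "we obtained a sample size of 14 subjects per group to detect a difference of 0.8 between the means of each group", by a two-sided independent-samples t-test at 80% power. The basis is described as unpublished preliminary ECSP-I data. No expected mean is given for any group.

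Section 2.11 (Study procedures) defines the groups. Group 2 consists of "infants with no signs of concern (scores at the Griffiths-3 and CSBS-ITC in the normal range) which are siblings of ASD children". Group 1 meets the same requirement on the same two instruments, but the older sibling is typically developing. Group 3 needs a Griffiths-3 quotient below 85 together with at least one CSBS-ITC score in the concern range.

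Hypothesis H3 in section 1.1.2 expects differences between the groups at baseline, but does not say how large.

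**The concern.** The three pairs are not alike. Two of them set infants with signs of concern against infants without. The third sets two sign-free groups against each other, separated at entry by sibling status. Section 2.6 gives all three the same separation of 1.43 SD, and a reader of the power statement cannot tell that it is much more demanding for one pair than for the others.

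What is at stake is how a non-significant Group 1 versus Group 2 result is read. Beside an unqualified 80%, it could be taken as evidence that sign-free siblings of children with ASD resemble sign-free siblings of typically developing children. With 14 per group that reading is safe only if the difference worth finding is close to 0.8.

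A second, smaller matter is the per-test level. With three groups there are three pairs, and 0.01 is stricter than Bonferroni requires for three. This costs power in every comparison, including those with Group 3.

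**Working it through.** **Inputs.** From section 2.6: difference 0.8, SD 0.56, two-sided alpha 0.01, power 80%, 14 evaluable per group. Assumed here: normal data, equal variances, and an overall error rate of 5% (the article does not state the overall rate).

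**1. Reproducing the plan's figure.** Standardised difference: 0.8 / 0.56 = 1.43. For a two-sample t-test with n per group, df = 2n − 2 and noncentrality = difference / (SD × √(2/n)).
- n = 14: 0.8 / (0.56 × √(2/14)) = 3.78, df 26, critical t 2.779, power 83.1%.
- n = 13: noncentrality 3.64, df 24, critical t 2.797, power 79.2%.

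So 14 is the smallest number per group that reaches 80%. The stated figure is correct.

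**2. What it takes for all pairs to reach 0.8.** Order the three means. The outer gap is the sum of the two adjacent gaps. If both adjacent gaps are at least 0.8, the outer gap is at least 0.8 + 0.8 = 1.6, and 1.6 / 0.56 = 2.86 SD. With means 0, 0.8 and 1.6, each adjacent pair has 83% power and the outer pair more than 99%. If instead the outer gap is 0.8, at least one adjacent gap is 0.4 or less.

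**3. Power for one pair if its true difference is smaller** (same formula, n = 14, alpha 0.01). The differences are illustrative; the article gives none.

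| True difference | In SD | Power | n per group for 80% |
|---|---|---|---|
| 0.8 | 1.43 | 83% | 14 |
| 0.6 | 1.07 | 53% | 23 |
| 0.4 | 0.71 | 21% | 48 |
| 0.2 | 0.36 | 5% | 185 |

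If all 16 enrolled per group are evaluable, power is 89% at 0.8 and 25% at 0.4.

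**4. The per-test level.** Bonferroni for three pairs at an overall 5% is 0.05 / 3 = 0.0167. At that level, 14 per group gives 88% power at 0.8. Under equality of all three means, simulation puts the chance of any significant pair at about 2.8% for three tests at 0.01 (runs gave 2.7% to 2.8%).

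**5. A closed procedure on the same 14 per group.** A global F test at 5% comes first, and each pairwise t-test at 5% counts only if the F test is significant. Simulation, 100,000 or more runs per setting:

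| True means (Groups 1/2/3) | Comparison | Three tests at 0.01 | Closed procedure |
|---|---|---|---|
| 0/0/0 | any false positive | about 2.8% | 5.0% |
| 0/0/0.8 | each Group 3 pair | 83% | 94% |
| 0/0.4/0.8 | the 0.8 pair | 83% | 91% |
| 0/0.4/0.8 | each 0.4 pair | 21% | 44% |

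When exactly two means are equal, only one null hypothesis is true and it is tested at no more than 5%. With three groups the procedure therefore controls familywise error in every configuration.

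**6. Precision for Group 1 versus Group 2.** Expected 95% half-width with 14 per group: 2.056 × 0.56 × √(2/14) = 2.056 × 0.2117 = 0.44.

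**The case against.** The strongest reply is that a power statement is conditional. Section 2.6 names a difference to detect; it does not predict that the three means lie exactly 0.8 apart. Any pair that truly differs by 0.8 or more has at least the stated power. This stands in full. A reader might infer from the geometry that the stated power must fail for at least one comparison. The article does not support that inference, because means at 0, 0.8 and 1.6 satisfy every pair.

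A reader might also conclude that the 80% can hold only for comparisons with Group 3. That is not shown either. Groups 1 and 2 are selected on Griffiths-3 and CSBS-ITC, not on an ECSP-I cut-off. By T1 and T2, Group 2 has had active monitoring and Group 1 has not. H3 expects baseline differences, and the preliminary data behind the calculation are not visible. The 0.8 is unsupported for this pair, not refuted.

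Three further points are fair:
- The 0.4 spacing is an illustration, not a figure from the article.
- The article claims no joint power. The chance of about 67% that all three tests are significant at means 0/0.8/1.6 therefore contradicts nothing in it.
- The article does not say that a non-significant result will be read as equality.

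On multiplicity, Bonferroni is valid, and part of the closed procedure's gain only undoes the use of 0.01: at 0.05/3 power is already 88%. The remaining step, from 88% to 94% or 91%, belongs to the closed procedure itself.

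**Conclusion.** The sample size is computed correctly and the 80% is true on its stated condition. The weakness is that one 1.43 SD difference is carried over to Group 1 versus Group 2 with nothing in the article to support it. All pairs meet the condition only if the outer groups are at least 2.86 SD apart. If Groups 1 and 2 differ by less than 0.8, power for that comparison falls to 53% at 0.6, 21% at 0.4 and 5% at 0.2. Which of these applies cannot be settled from the article.

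Separately, 0.01 per pair is stricter than three comparisons require. On the same participants, the closed procedure raises Group 3 power at a 0.8 difference from 83% to about 94% if Groups 1 and 2 are equal, or to about 91% for means 0/0.4/0.8, with familywise error at about 5% within a time point. These figures rest on normal data, a common SD of 0.56, 14 evaluable per group and an intended overall 5%. They say nothing about error across the three time points.

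**What to change.** 1. In section 2.6, state that the 80% applies to a pair whose true ECSP-I difference is 0.8. Add power for smaller Group 1 versus Group 2 differences, using the table above or values drawn from the preliminary data. State that this comparison will be reported as an estimate with a confidence interval, and that a non-significant test will not be presented as showing equality.
2. Within each time point, replace the three tests at 0.01 by the closed procedure for three groups: a global F test at 5%, then pairwise t-tests at 5% only if the F test is significant.

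The cost is a rewritten paragraph and one extra test per time point, with no change in enrolment or data collection. The drawbacks are that simultaneous confidence intervals are less direct under a closed procedure than under Bonferroni, and that the power statement for Group 1 versus Group 2 will look less favourable. If the sponsor prefers to keep Bonferroni, using 0.05/3 recovers part of the gain (88% at 0.8).
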